#### **16b. Allocation concealment mechanism**

The same researcher who performed the randomization process will seal the opaque envelopes containing the group that each participant will be allocated and deliver to the main researcher.

#### **16c. Implementation**

The sequence of allocation and enrollment of participants will be done by an independent researcher and the assignment of participants to interventions will be done by the main researcher.

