### **13. Participant timeline**

Registration will remain open until the sample size is reached. Next, a week will be reserved for the initial assessments (pre-intervention), followed by eight weeks of intervention. Finally, in the following week, the final evaluations (post-intervention) will be carried out.

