## **METHODS: ASSIGNMENT OF INTERVENTIONS (FOR CONTROLLED TRIALS)**

### **16. Allocation**

**16a.** Sequence generation: The randomization process will be carried out by a blinded researcher who is not part of the study team. Random numbers will be generated by online software (randomization.com), which will distribute participants into two groups of equal size (1:1).

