### **26. Consent or assent**

**26a.** The principal investigator will obtain informed consent from each participant. For this, he should explain in clear language all aspects of the study, such as: evaluation measures, intervention procedures, risks and benefits. In addition, a Consent Term approved by the Ethics Committee that approved the study must be read by the participant, who must sign the document if he/she wishes to participate in the study.

**26b.** If it is necessary to use the image of a person demonstrating the exercises of the intervention protocol, an informed consent will also be required specifically for this purpose.

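### Section 16c gives the allocation sequence and enrolment to one researcher, and nothing says the list is made only after registration closes, so allocation concealment is undermined

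*Protocol*

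**What the plan says.** Four parts of the protocol assign roles at entry.

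- Section 16a: "The randomization process will be carried out by a blinded researcher who is not part of the study team". Online software produces the random numbers, with 1:1 allocation.
- Section 16b: "The same researcher who performed the randomization process will seal the opaque envelopes containing the group that each participant will be allocated". That person then hands the envelopes to the main researcher.
- Section 16c: "The sequence of allocation and enrollment of participants will be done by an independent researcher", whereas "the assignment of participants to interventions will be done by the main researcher".
- Section 26a: "The principal investigator will obtain informed consent from each participant".

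On timing, section 13 says: "Registration will remain open until the sample size is reached". A baseline week, eight weeks of intervention and a final assessment week follow. Section 27 has participants numbered from randomization onwards. No section states when the list is generated relative to registration, or when the envelopes are opened relative to the baseline tests.

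**The concern.** Allocation concealment requires that whoever decides on entry cannot know the next allocation. Section 16c names one person for the list and for enrolment. If that person has the list while volunteers are still being accepted, ordered or turned away, the decisions can follow the allocation, knowingly or not.

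Three features of this trial make the safeguard important. Section 17a says that participants and therapists cannot be blinded, so concealment is a main protection against selection into arms. Section 14 plans 16 per group, so a few steered entries could matter. The ANCOVA in section 20a adjusts for baseline data, which would absorb imbalance in the measured score but not in motivation, expected adherence or trainability.

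Who makes the list and who enrols are protocol matters, and 16c states them positively. This is a role fixed badly, not a detail left for a statistical analysis plan.

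**Working it through.** No figure in the protocol bears on this point, so the check sets the sections side by side.

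**Step 1: who does what.**

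| Task | Person named | Section |
|---|---|---|
| Generate the list | Blinded researcher outside the study team | 16a |
| Fill and seal envelopes | The same researcher as in 16a | 16b |
| Hold envelopes | Main researcher | 16b |
| Allocation sequence and enrolment | An independent researcher | 16c |
| Assign participants to interventions | Main researcher | 16c |
| Obtain consent | Principal investigator | 26a |

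**Step 2: is it one person?** Section 16c by itself puts the sequence and enrolment together. Linking that person to 16a and 16b is an inference, but the natural one: both 16a and 16c say who produces the sequence, and both describe someone outside the team. If they were two people, the protocol would name two different makers of the same list.

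**Step 3: does *blinded* or *independent* cure it?** No. Section 16a does not say what the researcher is blinded to, and it cannot be the list that this person generates. Independence lowers the motive to steer but does not remove the knowledge.

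**Step 4: does the timing cure it?** The protocol allows either of two orders.

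- *List made while registration is open.* The enroller can know coming allocations while deciding who enters and in what order. The envelopes do not prevent this.
- *List made after registration closes.* There is no allocation to foresee at entry. What remains is the matching of people to list positions: section 27 numbers participants from randomization without saying who does so or by what rule, and the person who met the volunteers would also hold the list.

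Section 13 is compatible with both orders, because it says when registration ends but not when the list is made.

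**Step 5: what do the envelopes still protect?** They hide the allocation from the main researcher, who receives them sealed and assigns participants. That protection stands under either order.

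**Step 6: opening the envelopes.** Section 10 lists inability to perform the pre-intervention assessment as an exclusion, while 18b has every randomized participant analysed. If envelopes were opened before baseline, such a person would be randomized but have no baseline value for the ANCOVA covariate (20a) or for the carry-forward (20c). The protocol does not say that this order is intended; it leaves the order open. The rewording can close this gap too.

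**The case against.** The strongest reply is that the trial looks like a batch design. Registration runs to the full sample, the software distributes participants into two groups, the envelopes hold the group for each participant, and numbering starts at randomization. All this fits randomizing a cohort already assembled, in which case the enroller has nothing to foresee. This stands as a plausible reading, and it is why one cannot say that the enroller knows the list at entry. It does not dispose of the point, because the protocol never states the order and a safeguard should not rest on inference.

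Other parts of the reply also stand. Section 16c says *an* independent researcher, although 16b says *the same* researcher when it means that, so the identity is likely but not certain. Consent by the principal investigator (26a) and enrolment by someone else can coexist, so 26a calls for clearer roles and is not a contradiction. An outsider with an enrolment task sits awkwardly with 16a, but both sections agree that the person is independent.

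A reader might infer that concealment is defeated outright. The documents do not support that: it would need the list to exist during entry decisions, which is not stated, and it would ignore the protection that the envelopes give against the main researcher. A reader might also want the bias in standard deviations. That would need an assumed number of steered participants and an assumed difference in training response between them, and the protocol gives a basis for neither.

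**Conclusion.** The point holds as a weakness in stated roles. Section 16c puts the sequence and enrolment in one pair of hands, and the protocol does not rule out that the list exists while entry is being decided. Concealment is undermined, not necessarily defeated.

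The size of any bias cannot be estimated from the document; it could be nil if the list is made after the cohort is closed and numbers are assigned by a fixed rule.

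The conclusion rests on two assumptions: that the independent researcher of 16c is the outside researcher of 16a and 16b, and that the unstated order leaves early list generation possible. If the first failed, 16c would still join the sequence with enrolment. If the second failed, foreknowledge at entry would disappear, and only the matching of people to list positions would need fixing. The change should be made because the trial is unblinded and small and the remedy costs almost nothing.

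**What to change.** Rewrite 16c in one of two ways.

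1. **Separate the roles.** The independent researcher only generates the sequence and prepares sequentially numbered, sealed opaque envelopes, with no part in recruitment, eligibility or enrolment. A study-team member without access to the list enrols.
2. **Fix the order.** The sequence is generated only after all participants are registered, confirmed eligible and baseline-tested, with participant numbers fixed beforehand. Section 27 would then need to say that numbering precedes randomization.

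Under either option, state that envelopes are opened in number order after the baseline assessment is recorded, and align 16a, 16c and 26a on who generates, enrols, consents and assigns. Section 16a should also say what its researcher is blinded to.

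The cost is wording, recorded through the amendment route in section 25. No extra visits or participants are needed, the staff are those the plan already relies on, and section 13 already completes registration before the baseline week. If enrolment has already taken place, rewording cannot change what was done; the report should then state who enrolled, when the list was generated and when the envelopes were opened.

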### **17. Blinding (masking)**

**17a.** As this is a clinical trial involving physical exercise, it will not be possible to blind participants and therapists. Only the rater is expected to be blind.

**17b.** To test whether the evaluator was really blind, the main researcher should question the evaluator after the evaluations regarding the allocation of each participant.

## **METHODS: DATA COLLECTION, MANAGEMENT, AND ANALYSIS**

### **18. Data collection methods**

**18a.** Data collection will be carried out by an experienced evaluator, a professional with a degree in Physiotherapy and Physical Education. The tests performed and their measurement properties are described below:

*Muscle strength of the knee extensors and flexors* – It will be evaluated using elastic bands (Thera Band GmbH, Hadamar, Germany) as previously described [23]. Participants will be tested on their dominant side. After a 10-minute warm-up on a cycle ergometer (60 rpm, 80 W), participants will be positioned on the seat of a standardized chair. Participants will be asked to perform the maximum number of repetitions with an elastic band of intermediate resistance (black color). If they managed to perform 11 repetitions, an elastic band of greater resistance will be selected for the next attempt. This procedure will be repeated (maximum of 5 attempts with 5 minutes of rest between attempts) until the participant is able to perform 10 or fewer repetitions. The following prediction equation will be used:  $1\text{-RM} = \text{resistance in kg} / (1.0278 - [0.0278 \times \text{reps}])$  [24]. This test demonstrated high validity against concentric peak torque measured by an isokinetic dynamometer ( $r = 0.93$ ) and test-retest reliability ( $\text{ICC} \geq 0.98$ ,  $\text{CV}[\%] \leq 3.44$ ) [23].

*Vertical jump* – The countermovement jump test (sargent jump) will be used as an indicator of lower limb muscle power. The objective of the test will be to verify the highest height at the peak of the vertical jump, measuring two points marked on the wall by the participant himself, with the fingers of one of the chalk-stained hands: (1) the initial measurement will be obtained with the participant standing and erect, keeping the dominant arm extended parallel and above the head, marking the wall with chalk as high

as possible, keeping the soles of the feet completely in contact with the ground; (2) the second measurement will be obtained with the participant touching the wall with the fingers of the hand as high as possible during the peak of the vertical jump. Three attempts will be allowed with a two-minute interval between them, with the highest value in centimeters being recorded among the three attempts. This test demonstrated high validity ( $r = 0.99$ ) and test-retest reliability ( $r = 0.99$ ) [25].

*Handgrip strength* – To determine handgrip strength, a digital hydraulic dynamometer (Saehan SH1001) will be used. The participant must be seated, with the spine erect and the knees flexed at  $90^\circ$ . The dominant upper limb tested will be positioned with the shoulder in adduction and neutral rotation, wrist in neutral position and elbow at a  $90^\circ$  angle. Participants will be instructed to perform three repetitions of maximum contraction maintained for five seconds, with a 60-second interval between each repetition. The maximum voluntary contraction will be determined by the highest value obtained in the three attempts. This instrument demonstrated excellent validity ( $r \geq 0.97$ ) and test-retest reliability ( $r \geq 0.98$ ) [26].

*Abdominal muscle endurance* – To assess abdominal muscle endurance, the 1-minute sit-up test will be performed. In dorsal decubitus, the participant should flex the knees, keeping the soles of the feet in contact with the ground, with the feet apart at a distance identical to the width of the hips. Her arms should be crossed over her chest. The evaluator will place his hands on the participant's feet to keep them in permanent contact with the ground. At the signal emitted by the evaluator, the participant will raise the torso until the anterior face of the forearms comes into contact with the thighs, immediately returning to the initial position, with contact of at least the anterior half of the scapulae on the ground. These movements should be repeated over one minute. The objective of the test will be to try to perform as many executions as possible in the stipulated time. This test demonstrated high test-retest reliability ( $ICC = 0.91$ ) [27].

*Muscular resistance of the trunk extensors* – To assess the muscular resistance of the trunk extensors, the Sorensen test will be used. The participant must be in ventral decubitus with the lower extremity of the body attached to a stretcher, with the region of the anterior superior iliac crest demarcating the final point of support. Before starting the test, the participant will be allowed to support the upper extremity of the body, located outside the stretcher, on a chair. The test will start when the participant raises the trunk and remains without touching the chair, with arms crossed in front of the chest, and keeping the trunk parallel to the ground as long as possible. The test will be stopped when the participant is unable to sustain the position or is prompted more than 2 times to align the trunk and maintain the neutral position. This test demonstrated moderate to high test-retest reliability in healthy adults ( $ICC \geq 0.76 \leq 0.97$ ) [28].

*Flexibility* – To assess the flexibility of the posterior region of the body, the sit-and-reach test with the Wells bench will be used. The participant must sit facing the bench, with bare feet, knees extended and soles of the feet in contact with the bench. The participant should extend her arms over the surface of the bench, with her hands positioned one over the other, coinciding with the tip of her middle fingers. Anterior trunk flexion will be requested, keeping the arms extended and the hand touching the measurement scale, trying to reach the greatest possible distance in a slow movement and without jerks. For

the purpose of the final result of the test, the greatest distance achieved in the series of three attempts will be computed. This test demonstrated high test-retest reliability ( $r = 0.98$ ) [29].

*Affective valence* – Assessment of affective valence will be performed by the Feeling Scale, which ranges from +5 (very good) to -5 (very bad). Positive values represent pleasure, while negative values represent displeasure. The answers will always be collected at the end of the exercise sessions. The adapted version of this scale for the Brazilian population showed high reproducibility ( $ICC = 0.64$ ) [30].

**18b.** All randomized participants will be evaluated post-intervention considering the group to which they were initially allocated. All initially randomized participants will be analyzed post-intervention. An intention-to-treat analysis is therefore planned.

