### 11. Interventions

**11a.** Intervention 1 – Traditional Pilates: This group will perform a traditional Pilates session, which consists of stretching exercises, followed by exercises to strengthen the core (trunk flexors and extensors), lower limbs and upper limbs. The total duration of the intervention in this group should be approximately 50 minutes.

Intervention 2 – Pilates without stretching: This group will conduct a non-traditional Pilates session. This is because stretching exercises will be excluded. The muscle strengthening exercises will be the same as in the TP group, so that it is possible to discuss the influence of the inclusion/exclusion of stretching for the considered outcomes. The total duration of the intervention in this group should be approximately 35 minutes.

**11b.** a participant must discontinue the intervention when at his own request (personal reasons), or due to any health problem that makes its continuity unfeasible (eg appearance of injury).

**11c.** adherence monitoring will occur through an attendance/absence form.

**11d.** all participants will be instructed to maintain their usual routine, especially with regard to physical activity and eating habits.

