### 12. Outcomes

- Change in muscle strength of knee extensors and flexors [Time Frame: Pre (baseline) and post-intervention assessment (after 8-weeks)]. Assessment of muscle strength with elastic resistance
- Change in strength/endurance by 1-minute sit-up test [Time Frame: Pre (baseline) and post-intervention assessment (after 8-weeks)]. Assessment of abdominal muscle strength/endurance in 1-minute
- Change in muscle strength by handgrip test using hand dynamometer [Time Frame: Pre (baseline) and post-intervention assessment (after 8-weeks)]. Assessment of handgrip muscle strength
- Change in the muscular resistance of the trunk extensors by the Sorensen test [Time Frame: Pre (baseline) and post-intervention assessment (after 8-weeks)]. Assessment of the muscular resistance of the trunk extensors (Sorensen)

- Lower limb muscle power [Time Frame: Pre (baseline) and post-intervention assessment (after 8-weeks)]. Assessment of lower limb muscle power by vertical jump
- Flexibility [Time Frame: Pre (baseline) and post-intervention assessment (after 8-weeks)]. Flexibility assessment by the sit-and-reach test
- Affective valence [Time Frame: The scale will be applied at the end of each exercise session, over the 8 weeks, 3x a week, thus totaling 24 assessments throughout the study.]. Assessment of affective valence by the Feeling Scale. It ranges from +5 (very good) to -5 (very bad). Positive values represent pleasure, while negative values represent displeasure.

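### Read literally, section 18a sends the blinded rater to the end of every exercise session to collect the Feeling Scale, which puts the trial's only masking at serious risk

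*Protocol*

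**What the plan says.** Four parts of the protocol bear on this.

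- **Section 17a (Blinding)** explains that participants and therapists cannot be masked in an exercise trial, and continues: "Only the rater is expected to be blind". Section 17b calls this person the evaluator and has the main researcher ask, once the evaluations are over, about each participant's allocation.
- **Section 18a (Data collection methods)** opens with "Data collection will be carried out by an experienced evaluator, a professional with a degree in Physiotherapy and Physical Education" and goes on: "The tests performed and their measurement properties are described below". The list that follows covers knee strength, vertical jump, handgrip, sit-ups, the Sorensen test, sit-and-reach and, last, affective valence by the Feeling Scale. For that scale it states: "The answers will always be collected at the end of the exercise sessions".
- **Section 12 (Outcomes)** fixes the frequency: "The scale will be applied at the end of each exercise session, over the 8 weeks, 3x a week, thus totaling 24 assessments".
- **Section 11a (Interventions)** gives the session lengths. For traditional Pilates: "The total duration of the intervention in this group should be approximately 50 minutes". For Pilates without stretching: "The total duration of the intervention in this group should be approximately 35 minutes".

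No section names a different collector for the Feeling Scale, and none bars the evaluator from the sessions.

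**The concern.** Six of the seven outcomes are measured before and after the intervention. For those six, a rater who stays out of the intervention period can plausibly remain blind. The Feeling Scale is different because it is collected inside the intervention, session by session. If the evaluator named in 18a collects it, the one person who must not know the allocation meets every participant repeatedly, in the place where the allocation is being delivered, before the post-test.

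Rater blinding is the only masking the trial has. Two post-tests leave clear room for the rater to influence the result. The Sorensen test is stopped on the rater's judgement that the position is lost or after more than two prompts to realign. In the sit-up test the rater holds the feet and gives the signal, and a repetition counts only if certain body contacts are made. If blinding fails, a group difference on these tests can no longer be attributed to stretching alone.

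**Working it through.** **Step 1. Who collects the scale?** Section 18a names one collector, the evaluator, and makes no exception. The Feeling Scale stands in the same list, in the same format as the other measures and with its own reproducibility figure. The sentence on the scale itself is passive and names nobody, and section 12 names nobody either. On a literal reading the evaluator collects it. On the most generous reading the collector is unspecified.

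**Step 2. How often?** Section 12 gives 8 weeks and 3 sessions a week: 8 × 3 = 24, which reproduces the stated 24 assessments per participant. With the planned 16 per group there are 32 participants, so at most 24 × 32 = 768 end-of-session contacts under full attendance and no dropout. This is a count of contacts, not of unblindings. An allocation can be learned only once per person, so at most 32 can be revealed.

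**Step 3. What could reveal the arm?** From section 11a:

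| | Traditional Pilates | Without stretching |
|---|---|---|
| Stretching | yes, before strengthening | no |
| Strengthening | same exercises | same exercises |
| Session length | about 50 min | about 35 min |

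The difference in length is 50 − 35 = 15 minutes. Someone who arrives only at the end would see the same strengthening work in both arms. The possible cues are therefore session length (if start times are known), seeing earlier parts of a session, and remarks by unblinded participants. The protocol does not say when or where each arm trains, so the strength of these cues cannot be determined.

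**Step 4. What protects the rater?** Only 17b, which acts after the evaluations. It can show that blinding was lost but cannot prevent or repair the loss.

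**Step 5. What could a loss of blinding do?** The documents give no size for rater bias, so the shifts below are assumptions. Take a two-sided t-test at 5%, n = 16 per group, df = 30, critical value 2.042, true difference zero, and a rater-induced shift δ in SD units. The noncentrality is δ × √(n/2) = δ × √8.

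| Assumed shift δ | Noncentrality | Chance of a false positive |
|---|---|---|
| 0 | 0 | 5.0% |
| 0.10 SD | 0.283 | 5.9% |
| 0.25 SD | 0.707 | 10.5% |
| 0.40 SD | 1.131 | 19.5% |

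This is for a single comparison and ignores the baseline adjustment of the planned ANCOVA. It shows scale only and is not evidence that such a shift would occur.

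**The case against.** The strongest reply is that no sentence actually gives the Feeling Scale to the evaluator. The assignment is inferred from the general opening of 18a. Where the evaluator has a hands-on role, as in the sit-up test, the text says so. Section 13 places the initial and final evaluations in their own weeks, outside the eight weeks of intervention. The scale is self-reported, and therapists are present at the sessions anyway. Collection by a therapist or by self-completion is compatible with the text.

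This stands in part. A reader might infer that 17a and 18a cannot both be followed, or that following the protocol necessarily unblinds the rater. The documents support neither reading. Both sections can be honoured if someone else collects the scale. Even if the evaluator does collect it, stretching comes at the start of a session, so a person present only at the end need not see it, and the cue from session length depends on scheduling that is not described.

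Three further limits also stand:

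- Several tests leave little room in the reading itself. The participant marks the jump on the wall, handgrip is read from a dynamometer, and reach is read from a scale. There the rater could mainly affect effort.
- The protocol states no directional hypothesis. Its objective is to verify effects, and its background treats harm or benefit as unknown, so no direction of bias can be presumed.
- The 17b check means that a loss of blinding need not go unnoticed.

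What the reply does not remove is that the only collector named is the blinded evaluator, that no safeguard separates this person from the sessions, and that one permitted way of running the trial endangers its sole masking.

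**Conclusion.** The point holds as a serious, avoidable risk and not as a demonstrated loss of blinding. It rests on reading the opening of 18a as covering the whole list beneath it, which is the plain reading but not the only possible one. It also rests on the session differences in 11a and the participants' knowledge of their arm being usable cues, which is plausible but depends on undescribed scheduling. The exposure is greatest for the Sorensen and sit-up tests and smaller for jump, handgrip and reach. The size of any bias is unknown; the range of 5.9% to 19.5% follows only from the assumed shifts. This should be fixed, with moderate confidence. It concerns the conduct of the trial, so it is not something that a separate analysis plan would be expected to settle.

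**What to change.** **In 18a:** state that participants complete the Feeling Scale themselves, on a form carrying only their study number, and that session staff collect it, not the blinded evaluator.

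**In 17a:** state that the evaluator does not attend sessions and does not see session forms (attendance or Feeling Scale) before the last post-test, and that participants are asked at the post-test not to mention their sessions. Keep the 17b check as it is.

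**Cost:** a few sentences and one paper form. No extra staff should be needed, because therapists are already at the sessions and attendance (11c) and the adverse-event question (22) already call for recording there. One small downside is that unblinded staff then collect the scale. Since unblinded participants report it themselves in any case, little is lost.
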